## Abstract

**Background:** Out-of-hospital cardiac arrest (OHCA) survivors and their relatives may face challenges following hospital discharge, relating to mood, cognition, and returning to normal day-to-day activities. Identified research gaps include a lack of knowledge around what type of intervention is needed to best navigate recovery. In this study, we investigate the feasibility and patient acceptability of a new virtual psychoeducational group intervention for OHCA survivors and their relatives and compare it to a control group receiving a digital information booklet. **Methods:** V-CARE is a comparative, single-blind randomized pilot trial including participants at selected sites of the STEPCARE trial, in the United Kingdom and Sweden. Inclusion criteria are a modified Rankin Scale (mRS) ≤ 3 at 30-day follow-up; no diagnosis of dementia; and not experiencing an acute psychiatric episode. One caregiver per patient is invited to participate optionally. The intervention group in V-CARE receives four semi-structured, one-hour-long, psychoeducational sessions delivered remotely via video call by a trained clinician once a week, 2–3 months after hospital discharge. The sessions cover understanding cardiac arrest; coping with fatigue and memory problems; managing low mood and anxiety; and returning to daily life. The control group receives an information booklet focused on fatigue, memory/cognitive problems, mental health, and practical coping strategies. **Results:** Primary: feasibility (number of patients consented) and acceptability (retention rate); secondary: satisfaction with care (Client Satisfaction Questionnaire 8 item), self-management skills (Self-Management Assessment Scale) and, where available, health-related outcomes assessed in the STEPCARE Extended Follow-up sub-study including cognition, fatigue, mood, quality of life, and return to work. **Conclusions:** If preliminary insights from the V-CARE trial suggest the intervention to be feasible and acceptable, the results will be used to design a larger trial aimed at informing future interventions to support OHCA recovery.

## 1. Introduction

Every year more than 300 000 individuals in Europe suffer an out-of-hospital cardiac arrest (OHCA); only around 8% of them survive to hospital discharge [1,2].

Most survivors make a ‘good’ recovery—that is, they achieve a quality of life akin to what they had prior to their OHCA—despite this, difficulties with cognition, mood, and physical recovery have been extensively documented. Cognitive deficits, albeit usually mild, affect as many as 40–50% of survivors 6–12 months after their cardiac arrest [3,4,5]. Impairments are often found in memory, followed by executive functioning and processing speed, although the heterogeneity of the measures and methodology used reduces the generalizability of these results [6,7]. Anxiety and depression have also been described in OHCA survivors, with a recent systematic review reporting symptoms of depression, anxiety and post-traumatic stress disorder (PTSD) in 19%, 26%, and 20% of patients, respectively [8]. Psychological distress has been found to contribute to fatigue severity one month after hospital discharge [9]; high psychological distress can also impact a variety of health behaviours and influence health-related quality of life and risk of cardiovascular disease [10,11]. Rates of fatigue, anxiety, depression, reduced mental function, and disability appear to be the same 1 and 5 years after the event, suggesting limited natural recovery [10]. Returning to daily activities and previous occupational roles is often problematic, with around half of survivors experiencing difficulties or the inability to resume work [12,13,14,15]; these rates remain lower compared to patients recovering from myocardial infarction [16].

Co-survivors, including family members and close friends of survivors, also undergo their own process of recovery. Qualitative studies show that this involves overcoming the initial shock of witnessing the arrest [17] and having to support the survivor in their recovery after discharge from hospital, often with little or no support from healthcare professionals [18]. Persistent symptoms of post-traumatic stress disorder (PTSD) and anxiety have also been documented to be common in this population [19,20,21]; however, no study thus far has assessed the impact of mental interventions to mitigate their psychological distress [22]. Recent research underlines that both survivors and co-survivors have a need for more resources and education on how to best navigate recovery after an OHCA [17,23].

### 1.1. Rationale for a Psychoeducational Intervention

Several questions remain unanswered around the psychosocial impact of survivorship on quality of life, as well as optimal post-discharge rehabilitation and care to maximize recovery for survivors and for their family members. In recent years there has been broad recognition of the importance of providing follow-up for survivors of OHCA and their key supporters (hereby defined as family members, spouses, partners, or friends who provide support from admission to hospital through rehabilitation/recovery and beyond). One such example is a priority-setting exercise completed using the methodology developed by the James Lind Alliance, which identified that the needs of key supporters post-OHCA must be served better, as well as confirming the specific need for post-discharge survivor-focused care [24,25]. Similarly, a statement from the American Heart Association (AHA) also identifies a knowledge gap in cardiac arrest research concerning the role for support networks/groups after cardiac arrest [26]. Current guidelines and position statements all stress the importance of providing appropriate follow-up care, both to survivors and key supporters, whilst highlighting the lack of evidence-based interventions available [26,27,28].

Thus far, few studies have evaluated the impact of post-discharge support and educational interventions on longer-term quality of life. A recent systematic review and meta-analysis highlighted the lack of good-quality evidence and the high heterogeneity in intervention design and the outcome measures used; in addition, rehabilitation interventions have not been described in detail, preventing replication of results [29]. Of the studies published so far, the ‘Activity and Life after Survival of a Cardiac Arrest’ RCT showed significant benefits in the outcomes of cardiac arrest survivors, with additional analyses suggesting a high probability of cost-effectiveness from a societal perspective [30,31]. An intense 11-session individual psychological and education intervention was found to reduce risk of cardiovascular death; however, the impact on quality of life was not measured [32], and the volume and intensity of therapy provided may be a barrier to widespread adoption. A small pilot study focused specifically on chronic fatigue after OHCA showed that an energy-conservation and problem-solving therapy intervention (delivered over the telephone) was feasible, acceptable, and effective in improving outcomes [33]. More recently, a residential rehabilitation intervention focused on fatigue and physical/psychological consequences of an OHCA showed promising results in several domains, such as quality of life, fatigue, and anxiety, even though the high intensity/volume of this intervention may not make it suitable for widespread adoption [34]. A protocol for the remote delivery of individual psychotherapy and cardiac-focused psychoeducation combining mindfulness and exposure-based interventions has also recently been successfully trialled in a small sample of OHCA survivors experiencing PTSD [35]. Other trials focused on exploring interventions to facilitate return to work (ROCK trial [36]), alleviate psychological distress and improve cognitive abilities (ENFORCER trial [37]), and to promote recovery and self-management (CARESSf) [38] are currently ongoing.

The studies currently available suggest that a programme integrating educational elements and skill training (for example, for the management of fatigue) might be appropriate for improving outcomes after an OHCA [35]. To our knowledge, however, an intervention involving both survivors and key supporters, delivered virtually in a group format, has not been trialled yet. The feasibility and acceptability of this model require exploration; a virtual group intervention for elderly people with depression was found to be feasible and effective [39]; however, in another study, a tele-rehabilitation group intervention failed to recruit and retain participants in a geriatric population [40].

### 1.2. Study Aims

The primary aims are to investigate whether the Virtual Care After REsuscitation (V-CARE) intervention—a bespoke psychoeducational, remotely delivered intervention co-designed with cardiac arrest survivors and their key supporters—is feasible and tolerable 2 to 3 months post-discharge from hospital. A secondary aim is to explore whether participating in the V-CARE intervention leads to beneficial effects in self-management skills and higher satisfaction with the treatment received, compared to a control group receiving a digital information booklet only.

## 2. Methods

### 2.1. Study Design

This study, a comparative, single-blind randomized pilot trial investigating the psychoeducational V-CARE intervention, is included as a sub-study in the Sedation, TEmperature, and Pressure after Cardiac Arrest and REsuscitation (STEPCARE) trial, an international, multicenter, randomized, factorial, and superiority trial designed to evaluate optimal post-resuscitation care strategies for unconscious adult patients following OHCA. The study employs a 2 × 2 × 2 factorial design to assess three interventions, namely sedation strategy, temperature management, and mean arterial pressure targets [41]. The trial aims to enrol 3500 participants, with an estimated completion date of 30 June 2026.

The V-CARE study described here includes participants at selected sites of the STEPCARE trial, in the United Kingdom and Sweden, surviving with a good neurological outcome (mRS) ≤ 3. Patients will be recruited after the scheduled 30-day follow-up of STEPCARE.

### 2.2. Patient and Public Involvement

The development of the V-CARE intervention and of the digital information leaflet were informed by an exploratory sequential mixed-method design, engaging both OHCA survivors and their key supporters. This process involved two steps:(1)Running two semi-structured focus groups—one with survivors and one with key supporters—each lasting approximately 90 min, to gather in-depth insights from OHCA survivors and their key supporters regarding the ideal structure, content, and mode of delivery for the proposed psychoeducational intervention.(2)Themes emerging from the focus groups (Table S1) were used to develop a survey aimed at assessing the generalizability of the opinions expressed. This survey was distributed online via Sudden Cardiac Arrest UK and was available for one month between February and March 2022. A total of 95 responses were collected, comprising 62 survivors and 33 family members (70 women, 25 men). The survey included 26 questions, a mix of closed and open-ended items, to capture detailed feedback on the proposed intervention.

The V-CARE intervention and the digital information booklet were initially drafted by our research group. Feedback was then obtained from survivors and key supporters after draft versions were posted in the private Sudden Cardiac Arrest UK (SCA UK) Facebook group. Both the V-CARE intervention and the digital booklet were then translated into Swedish.

### 2.3. Study Population and Randomization

In addition to the criteria needed for taking part in STEPCARE, OHCA survivors eligible to take part in V-CARE are also required to have an mRS ≤ 3 at the 30-day follow-up and (a) must not have a diagnosis of dementia that would impact their ability to participate and benefit from the sessions and complete baseline/outcome measure (based on a clinician’s evaluation and/or self-report by the patient or family) and (b) must not be actively psychotic/experiencing any other serious acute mental health condition that would affect their participation in this study, based on clinical evaluation.

When recruited, consenting patients will be encouraged to take part in the study together with a ‘key supporter’; however, this will not be a requirement.

Consenting patients will be randomized on an equal basis (1:1) to the V-CARE arm or to the information booklet arm. V-CARE has a randomized block design with a separate randomization list in each country, completed by a local lead site. Custom-built software was developed using Python (v3.12.7) and the Tkinter library to allocate patients into two study conditions—V-CARE or the digital information booklet. A computer-generated pseudo-randomized list with 25 sets of 2 unique numbers per set was pre-generated using an online randomization tool [https://www.randomizer.org/] (accessed on 7 October 2024) to ensure an unbiased allocation process.

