#### 2.4.1. V-CARE (Virtual CAre After REsuscitation)

The intervention focuses on providing early cardiac-arrest-related education, promoting the development of coping skills, encouraging peer support, and signposting survivors and key supporters to relevant resources/services.

The V-CARE programme involves 4 structured sessions, one a week, each lasting around one hour, supported by PowerPoint presentations (File S1). The content focuses on providing education on cardiac arrest and secondary prevention, addressing practical problems (for instance, returning to driving, travelling, living with an implantable cardioverter defibrillator (ICD), etc.) and understanding/coping with fatigue, cognitive changes, and psychological difficulties. As multiple sites in each country are expected to take part in this study, groups will be formed as soon as 3 to 6 patients have been recruited, although smaller groups could be formed if required. Group size will usually be between 4 and 12 participants. The aim is for the intervention to be delivered early to each group, starting around 2 and 3 months after hospital discharge; however, it is expected that it may be delivered to some groups up to—but not beyond—6 months post-discharge.

Each session includes broadly equal time for presentation, questions, and discussion, with the aim of encouraging participants to develop self-management skills. A printout of the PowerPoint slides used in each session is provided in Supplementary Material.

A single, designated healthcare professional will serve as a facilitator for each group and will be present for all sessions, having been trained by the study team; it is anticipated that it will be delivered by either a clinical psychologist or an occupational therapist, but a clinical nurse specialist could also manage a group. A cardiologist or cardiology resident will attend the first session to answer generic, cardiac-arrest-related questions.

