#### 2.4.2. Digital Information Booklet

This intervention, also co-developed with a patient group, consists of an information booklet focused on providing information and coping strategies for fatigue, memory, low mood, anxiety, and cognitive problems after a cardiac arrest. Whereas the content is similar to that covered in the V-CARE arm, these patients are not included in a group and as such do not have access to peer support or to guided discussions and reflections as provided in the group setting. In this intervention arm, tolerability will be assessed by the proportion of participants who complete the post-intervention outcome measures; additionally, participants will be asked to self-report whether they read or used the booklet. A copy of this intervention is provided in the Supplementary Material (File S2).

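### The allocation list is built from fixed pairs, so anyone who sees a whole country list can know up to half of the allocations in advance

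*Protocol article*

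**What the plan says.** Protocol article, section 2.3, gives the ratio: "Consenting patients will be randomized on an equal basis (1:1) to the V-CARE arm or to the information booklet arm". It gives the structure: "V-CARE has a randomized block design with a separate randomization list in each country, completed by a local lead site". It then describes the list itself: "A computer-generated pseudo-randomized list with 25 sets of 2 unique numbers per set was pre-generated using an online randomization tool". The same sentence presents this as the means of making allocation unbiased. Custom software assigns patients to the two conditions.

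Section 2.1 calls the study "a comparative, single-blind randomized pilot trial investigating the psychoeducational V-CARE intervention", without naming the blinded party. Section 2.4.1 describes a live video programme: "A single, designated healthcare professional will serve as a facilitator for each group and will be present for all sessions". Section 2.4.2 says of the booklet arm that "these patients are not included in a group and as such do not have access to peer support". On sites, section 2.4.1 states: "As multiple sites in each country are expected to take part in this study". Section 2.6 sets the target at 50 or more randomised, 25 per arm.

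**The concern.** In a 1:1 block of 2, the first allocation fixes the second. Those who run the list, form the groups and send out booklets will see which arm a patient has entered, because the two arms look nothing alike. They can then know the next arm before the next patient is approached or entered.

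The stake is who ends up in which arm. Eligibility in section 2.3 rests partly on clinical judgement (dementia that would affect participation, acute mental illness), so there is room for a likely attender to be entered when the next place is V-CARE, or held back when it is not. That would affect:

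- the tolerability criterion, whose attendance element (at least 3 of 4 sessions) applies only to V-CARE patients;
- the satisfaction criterion, which is judged in the V-CARE arm alone;
- the exploratory comparisons between arms, which section 3 says will guide the choice of primary outcome and the power calculation for a larger trial.

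The block size is printed in the article, so it is not a detail left to a fuller document.

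**Working it through.** **Inputs.** From section 2.3: 25 sets of 2, two arms, 1:1, one list per country, run by a lead site. From section 2.6: 50 randomised, 25 per arm. The number of sites per country is not given and is treated as an assumption *m*.

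**Step 1: the plan's own figure.** 25 sets × 2 = 50 places, one per arm in each set, which gives 25 per arm. This reproduces the target. The words 'block size 2' do not appear, but no other sensible reading fits the block design, the 1:1 ratio and the total. The article does not say whether the 25 sets are divided between the countries or each country has its own 25; the share that is predictable hardly depends on this (step 3).

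**Step 2: allocations known with certainty.** In a 1:1 block of size 2b, the expected number of forced allocations is 2b/(b+1), a share of 1/(b+1), for someone who knows the block size and all previous allocations on that list.

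| Block size | b | Forced per block | Share |
|---|---|---|---|
| 2 | 1 | 1 of 2 | 50% |
| 4 | 2 | 1.33 of 4 | 33% |
| 6 | 3 | 1.5 of 6 | 25% |

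For the plan: 50 × 0.5 = 25 allocations.

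**Step 3: allocations guessed correctly.** With blocks of 2, the first of each pair is guessed at 50% and the second at 100%: (25 × 0.5 + 25 × 1)/50 = 37.5/50 = 75%. If the 50 are split as 25 per country, each list has 12 full pairs and one unpaired first place: (24 × 0.75 + 1 × 0.5)/25 = 18.5/25 = 74%, with 12 of 25 known for certain. This is why the figure of 25 of 50 is an upper limit.

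Simulating 10,000 sequences of 50 on one list, with the rule of guessing whichever arm is behind, gave 75% for blocks of 2, 70% for blocks of 4, 68% for blocks of 6, and 69% for a random mix of 4 and 6.

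**Step 4: recruiters who see only their own site.** Suppose *m* equal sites share a country list. Half of the allocations are second in a pair, and the first of that pair was at the same site with probability 1/m. The share guessed correctly is then 0.5 + 0.25/m: 75% for m = 1, 62.5% for m = 2, 58% for m = 3 and 55% for m = 5. This is generous to the recruiter, because it supposes that they can tell which of their own patients form a pair. Lead-site staff who see the whole list keep the full 75%.

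**Step 5: how little it takes to move a criterion.** With 25 patients in V-CARE, each counts for 100/25 = 4 percentage points. On the satisfaction criterion in section 2.6, 7 low scorers (28%) is green and 8 (32%) is amber.

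**The case against.** A reader might conclude that allocation concealment is lost outright. The documents do not support that. The first place in each pair stays at 50/50, and the second is certain only to someone who knows the previous allocation on that country's list. Several sites per country are expected, and recruiters away from the lead site may see only part of the sequence.

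A reader might also take it as stated that recruiting staff know the allocations. That is an inference from the nature of the arms. The article leaves open whether the person running the list is separate from those who approach patients, and an article may leave that to the full protocol.

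It is also tempting to say that staff could fill groups faster, since "groups will be formed as soon as 3 to 6 patients have been recruited", or that the consent rate is distorted. Neither follows. Each completed pair yields exactly one V-CARE patient whatever staff do, and smaller groups are allowed. The consent rate is counted over all eligible patients before allocation, and nothing shows a direction or size of distortion.

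Two further points have some weight. Section 2.3 randomises patients who have already consented, so consent comes before allocation; but a place that can be predicted is known before the approach is made, so this ordering does not remove the problem. And section 2.6 rules out conclusions on effectiveness, which limits the harm without protecting the progression criteria or the planning of the next trial.

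What remains is that the stated block size creates avoidable predictability.

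**Conclusion.** The point holds in a limited form. The article fixes a block of 2, and the second place in each pair is determined by the first: up to 25 of 50 allocations, with about 75% guessed correctly by anyone who sees a full country list. For recruiters limited to their own site the figure is about 55% to 62.5%, assuming two to five equal sites. The claim that the list secures unbiased allocation is therefore too strong.

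The block size rests on reading the 25 sets of 2 as permuted pairs, which the matching total of 50 supports. The risk also assumes that someone who sees the list can influence who is entered next; the article neither states nor excludes this. The documents do not show that bias has occurred. For a pilot that disclaims efficacy, this is a moderate matter that should be corrected because the correction is cheap.

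**What to change.** For the remaining allocations, regenerate each country list with block sizes that vary at random and are not disclosed, for example 4 and 6. Have the lists prepared and held by someone with no part in recruitment or group formation. Remove or qualify the statement that the present list makes allocation unbiased, and report how many patients were allocated under it.

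**Gain.** With 4 and 6 used equally often, even someone who knew each block's size would be certain of only (1.33 + 1.5)/(4 + 6) = 28% of allocations, against 50% now; with sizes undisclosed the share can be no higher. The share guessed correctly falls less, from 75% to about 69%. Most of the protection therefore comes from keeping the sequence away from those who recruit.

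**Cost.** Two lists to regenerate. A country that stops partway through a block of 6 could be out of balance by up to 6/2 = 3 patients, and accrual to the V-CARE groups would be slightly less even than one in every two. Outcomes and sample size are unchanged.
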